### 2.5. Data Collection and Management

#### 2.5.1. Plans for Assessment and Collection of Outcomes

Study staff will be trained to perform the study tests in the framework of this trial, and collect and record the study data. All study data will be firstly collected on paper source documents: paper CRFs) and subsequently entered into electronic e-CRFs. For this study, e-CRFs will be developed on Open Clinica software. This can be definite and entered remotely by using the internet or entered offline on a laptop and synchronized with the main database at a later time. The e-CRF will allow identification of the study, site, and patient; recording of the selection and inclusion of patients in the study, and recording of all data collected at each study site.

#### 2.5.2. Plans to Promote Participant Retention and Complete Follow-Up

The study is an ancillary study embedded in the PyraPreg trial and has the same sampling points as defined in the PyraPreg trial (day of screening and days 1, 2, 3, 7, 14, 21, 28, 35, 42, 49–56, and 63 of follow-up) and a plan to promote participant retention or to complete follow-up has been developed in detail for the Pyrapreg trial. Consequently, there is no need to design a new plan to promote participant retention or to complete follow-ups.

#### 2.5.3. Data Management

Project data management will be handled by the Institut de Recherche en Sciences de la Santé (IRSS) which has the required expertise in all components of data management of clinical trials and epidemiological studies. The data management office is located on the main campus of the Clinical Research Unit of Nanoro (CRUN). The CRUN data management currently manages more than 10 ongoing research projects, including clinical trials on treatments, vaccines, and other preventive interventions. Data will be stored at the central server located at CRUN. The central database will be managed by a dedicated data manager, who will run consistency checks and produce queries to be resolved. The final database will be obtained after the resolution of all queries and will be locked for statistical analysis.

In terms of archiving, the Principal Investigator will prepare and maintain a file containing the essential documents for the conduct of the trial. CRF, consent forms of each study subject, and other relevant documents will be archived for 5 years. Direct access to source data and documents relating to the trial will be granted to the sponsor for trial-related monitoring, audits and Ethics Committee review, and regulatory inspections when applicable.

#### 2.5.4. Confidentiality

Every possible measure to ensure that all personal data collected during the study will be appropriately protected will be taken. The collection of personal information will be restricted to meet the objectives of the study, and only data relevant to the execution of the study and interpretation of data will be collected. Collected information will be kept for a minimal time period, which is regulated by national or international law. All personal data collected during the study will be kept confidential. After the collection of blood samples, a numerical identifier will be assigned to each sample. None of the results will be published with individual name identification. At the end of the project, all names will be destroyed. All personalised data forms, signed informed consent forms and other personalised information will be kept under lock and will be available only to the project coordinator, principal investigators, and data managers. Information stored in the electronic database will be protected by unique usernames and passwords, which will be made only available to appropriate authorised personnel. Data entry will be checked independently on site by the research clinician and/or by the PI to ensure accuracy. The collected information will never be transferred to countries lacking appropriate data protection or made available without restriction to third parties that are not directly linked to the project.

Plans for collection, laboratory evaluation, and storage of biological specimens for genetic or molecular analysis in this trial/future use

Blood samples will be collected for molecular analysis by PCR, which is used as a reference test for the diagnostic procedures followed in this trial. This work will be restricted to the assessment of the presence of *Plasmodium* species only. There will be no analysis of human genetic material. Collected specimens could be used for future diagnostic test development and evaluation and explicit informed consent from study participants will be obtained for this.

### 2.6. Statistical Methods

#### 2.6.1. Statistical Methods for Primary and Secondary Outcomes

As mentioned above, the outcomes of the evaluations will be analysed using 2 × 2 tables (at 95% confidence intervals), and comparisons will be made with standard diagnostic procedures in place and qPCR as the accepted reference test. Positive and Negative Predictive Values will be calculated. The sensitivity and specificity of the mini-dbPCR-NALFIA are assumed to be at least 90% [23]. The utility of the mini-dbPCR-NALFIA to monitor treatment success (in terms of recurrent parasitemia) will be compared to qPCR. The association between the molecular test results obtained during the follow-up will be assessed using logistic regression models.

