## 2. Design/Methods

The trial design is presented below by following the SPIRIT guidelines. This trial is an ancillary study embedded in an EDCTP funded drug trial (Safety and Efficacy of a newly registered Artemisinin-Based Combination (Pyronaridine-Artesunate-PYRAMAX^®^) (PyraPreg [PACTR202011812241529]). The planned phase 3 diagnostic study consists of two components.

The first component will assess the diagnostic accuracy of the mini-dbPCR-NALFIA test for the diagnosis of malaria in pregnant women (**diagnostic screening part**). The study hypothesis for this component is: “mini-dbPCR-NALFIA will offer an improved diagnostic platform over microscopy and/or currently available RDTs for the detection of malaria infection in pregnant women”. This will be studied through a phase 3 diagnostic trial. Diagnostic performance will be assessed following the WHO/TDR guidelines for the evaluation of diagnostics [29] and the results will be reported according to STARD principles [30]. This phase 3 evaluation will screen pregnant women at the point of enrolment for the main PyraPreg trial for the presence of malaria in both Burkina Faso and DRC. Potential study participants (≥15 years of age, pregnant, able to provide informed consent) will be identified during their visits to the study health facility and asked to participate in the diagnostic study. Consequently, both malaria negative, as well as malaria positive (confirmed by the standard diagnostic practices in place), will be tested for this screening part of the study. An additional blood sample (finger prick blood), next to the clinical sampling performed in the framework of the PyraPreg project at the point of screening, will be collected from the same women. This sample will be analysed by mini-dbPCR-NALFIA (index test) and qPCR (as reference test). The results of the experimental diagnostic testing will not be used to make any decisions about the clinical management of pregnant women.

For the **treatment follow-up part** (second component), we will recruit the same women who have been recruited for the main PyraPreg trial (in Burkina Faso only) and who will be followed up for a period of 63 days. At each of their planned study visit (at days 1, 2, 3, 7, 14, 21, 28, 35, 42, 49-56, and 63) we will obtain an additional blood sample for qPCR and mini-dbPCR-NALFIA testing.

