#### 2.2.7. Outcomes

The outcome (for the diagnostic screening and treatment follow-up parts) will be reported according to STARD principles [30]. We will report sensitivity, specificity, negative, and positive predictive values (primary outcome) of the mini-dbPCR-NALFIA test. The outcomes of the evaluations will be further analysed using 2 × 2 tables (at 95% confidence intervals), and comparisons of the performance of the diagnostic test under investigation will be made with standard diagnostic procedures in place and qPCR as the accepted reference test to determine the agreement between different tests (expressed as kappa values) [29]. 

To determine the utility of the mini-dbPCR-NALFIA test in monitoring treatment efficacy, parasite clearance will be assessed by mini-dbPCR-NALFIA and compared with qPCR. 

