#### 2.2.9. Sample Size

The sample size for the diagnostic screening component has been calculated according to the expected disease prevalence in the Nanoro health centre catchment area to give adequate statistical power to test sensitivity and specificity [29]. Sample size calculation is based on a 95% confidence interval and using the following equation [29,30]: p +/− 1.96 × √[p(1 − p)/n] where p= sensitivity (or specificity) measured as a proportion and n = number of samples from infected people (or for specificity from non-infected).

The sample size calculation is further based on the estimated prevalence of malaria in pregnancy in the study area, which is around 25% [32]. Based on these assumptions, the following sample size has been determined: 555 cases need to be recruited for the screening component.

For the treatment follow-up component, we will be following the number of cases that are being planned to be recruited for the main PyraPreg trial. In this case, it is expected that we can follow-up with around 138 pregnant women who are under anti-malaria treatment for a period of 63 days.

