#### 2.6.4. Methods in Analysis to Handle Protocol Non-Adherence and Any Statistical Methods to Handle Missing Data

The study is an ancillary study embedded in the PyraPreg trial and has the same sampling points as defined in the PyraPreg trial. Only an additional blood sample will be collected at each visit for the test. In case missing data occur during a visit, the whole data set of a participant at this visit will be removed from the analysis. This removal will be compensated by a slight over recruitment in the number of study participants. Nevertheless, a missing visit will not affect the data analysis of other visits of the participant.

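### Follow-up accuracy and logistic regression are planned on 11 visits per woman without provision for within-woman correlation or falling positivity; if visits are pooled, intervals are too narrow and PPV/NPV describe no visit

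*Protocol article*

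**What the plan says.** **Sampling.** Section 2 (Design/Methods) takes repeated samples from the women in the treatment follow-up component: "at days 1, 2, 3, 7, 14, 21, 28, 35, 42, 49-56, and 63) we will obtain an additional blood sample". Counting days 49-56 once, that is 11 visits after screening. Section 2.2.9 gives the number of women: "it is expected that we can follow-up with around 138 pregnant women who are under anti-malaria treatment for a period of 63 days". Under section 2.1.2 all of them enter with a *P. falciparum* infection on microscopy.

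**Outcomes.** Section 2.2.7 opens by covering both components: "The outcome (for the diagnostic screening and treatment follow-up parts) will be reported according to STARD principles". It continues: "We will report sensitivity, specificity, negative, and positive predictive values (primary outcome) of the mini-dbPCR-NALFIA test". The same section plans kappa as a measure of agreement between tests, and compares parasite clearance by the index test with qPCR.

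**Methods.** Section 2.6.1 says that "the outcomes of the evaluations will be analysed using 2 × 2 tables (at 95% confidence intervals"), and assumes sensitivity and specificity of at least 90%. For the repeated results it says: "The association between the molecular test results obtained during the follow-up will be assessed using logistic regression models". Section 2.6.4 removes a participant's data for an incomplete visit, and adds that "a missing visit will not affect the data analysis of other visits of the participant".

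The article does not name the unit of analysis for follow-up, a method for repeated results from one woman, or whether tables are made by visit.

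**The concern.** There are three difficulties, all in the follow-up component.

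1. **Correlation.** Binomial intervals from a 2 x 2 table and the ordinary logistic model treat every record as independent. Repeated results from one woman are likely to be correlated. If her visits enter one table or model unadjusted, intervals are too narrow and p-values too small.
2. **Changing positivity.** All women start microscopy-positive and are then treated, so qPCR positivity should fall over the 63 days. PPV and NPV depend on positivity. One pooled pair would hide a low NPV at early visits and a low PPV at late ones, and the late visits are where recurrent parasitaemia is judged.
3. **Association against agreement.** The odds ratio between two tests can be large while many results disagree. It does not show whether the index test can stand in for qPCR when treatment is monitored, which is the secondary objective.

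At stake is how firmly the trial can claim that the test is suitable for monitoring treatment.

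**Working it through.** **Inputs from the protocol article:** 138 women (2.2.9); 11 visits (2); sensitivity and specificity 0.90 (2.6.1).

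**Assumed, because the article does not give them:** within-woman correlation (ICC) 0.1, 0.3 and 0.5; mean qPCR positivity over follow-up 34%; positivity of 95% at an early visit and 10% at a late one.

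**Step 1. The plan's own figure.** The only calculated sample size is 555, for screening. With the formula in 2.2.9, p = 0.90 and an assumed half-width of 0.05, n = 1.96² x 0.09 / 0.05² = 138.3 infected women. Dividing by 25% prevalence gives 553.2, or 556 if 138.3 is first rounded up to 139. The 555 is reproduced. It rests on one sample per woman, so the present point does not touch it. The 138 follow-up women come from the main trial's recruitment.

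**Step 2. Size of the data set.** 138 x 11 = 1,518 paired results at most.

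**Step 3. Visits entering each estimate.** Sensitivity uses qPCR-positive visits only, and specificity qPCR-negative visits only. At 34% positivity this is 11 x 0.34 = 3.7 and 11 x 0.66 = 7.3 visits per woman.

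**Step 4. Coverage if those visits are treated as independent.** Design effect DE = 1 + (m - 1) x ICC. True coverage of a nominal 95% interval = 2Φ(1.96/√DE) - 1. Equal cluster sizes are assumed.

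| Estimate | m | ICC | DE | √DE | Coverage |
|---|---|---|---|---|---|
| Sensitivity | 3.7 | 0.1 | 1.27 | 1.13 | 92% |
| Sensitivity | 3.7 | 0.3 | 1.81 | 1.35 | 85% |
| Sensitivity | 3.7 | 0.5 | 2.35 | 1.53 | 80% |
| Specificity | 7.3 | 0.1 | 1.63 | 1.28 | 88% |
| Specificity | 7.3 | 0.3 | 2.89 | 1.70 | 75% |
| Specificity | 7.3 | 0.5 | 4.15 | 2.04 | 66% |

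The √DE column is the factor by which the interval is too narrow.

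**Step 5. Predictive values at 0.90/0.90.** With positivity q, PPV = 0.9q / [0.9q + 0.1(1 - q)] and NPV = 0.9(1 - q) / [0.9(1 - q) + 0.1q].

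| q | PPV | NPV |
|---|---|---|
| 0.95 | 0.855/0.860 = 0.99 | 0.045/0.140 = 0.32 |
| 0.34 (pooled) | 0.306/0.372 = 0.82 | 0.594/0.628 = 0.95 |
| 0.10 | 0.090/0.180 = 0.50 | 0.810/0.820 = 0.99 |

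The pooled NPV of 0.95 would stand beside 0.32 at the early visit, and the pooled PPV of 0.82 beside 0.50 at the late one.

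**Step 6. Association against agreement.** The odds ratio between index test and qPCR is [sens/(1 - sens)] x [spec/(1 - spec)]. For illustration, at 0.80 and 0.80 it is 4 x 4 = 16, although one result in five disagrees with qPCR.

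**The case against.** The strongest reply is that the article never says that visits are pooled or assumed independent. Logistic regression includes GEE, random-effects and cluster-robust forms. The rule in 2.6.4 concerns missing data and fits visit-by-visit tables at least as well as a pooled one. Such tables hold one record per woman, so they have neither the clustering nor the pooled PPV/NPV problem. Choices of this kind are often left to an analysis plan, which is not shown here. This reply stands as far as it goes: a reader might infer that the plan does treat all visits as independent, but the text supports only the conditional statement.

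A second reply is that agreement is already planned, since 2.2.7 names kappa and covers both components. That is correct, so it would be wrong to say that the plan offers only an odds ratio. Still, kappa also varies with positivity, and its usual standard error also assumes independent records.

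A third reply concerns size. Putting all 11 visits into the design effect gives DE = 1 + 10 x ICC, and coverage of 83%, 67% and 58% at ICC 0.1, 0.3 and 0.5. A reader might quote those figures, but they overstate the effect on sensitivity and specificity, each of which uses only part of the visits. The relevant ICC is also the correlation of test errors given the qPCR result, for which the article gives no value.

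What remains is that the article does fix particular methods for repeated, time-varying data, and that in standard form those methods do not fit such data.

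**Conclusion.** The point holds in conditional form. The article assigns 2 x 2 tables, predictive values and unqualified logistic regression to results from about 138 women seen 11 times each, without provision for repeated results or for positivity that should fall after treatment. If visits enter one standard table or model, nominal 95% intervals would cover about 80-92% for sensitivity and 66-88% for specificity. Pooled PPV and NPV would match neither early nor late visits.

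The coverage figures rest on the assumed ICC range, 34% mean positivity and equal cluster sizes. The PPV/NPV figures rest on the protocol's 90%/90% and on assumed positivity at the two ends. The direction of each effect does not depend on the exact values, provided the correlation is positive and positivity falls.

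This should be fixed, but it is not critical: it concerns the secondary component only. A reader might infer that the trial's main accuracy results are compromised. They are not, because screening takes a single sample per woman.

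**What to change.** State in 2.6.1, or in the analysis plan before database lock, that:

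- sensitivity, specificity, and positive and negative agreement with qPCR during follow-up are reported by visit, with exact or Wilson intervals;
- any estimate or logistic model across visits uses GEE with robust variance clustered on the woman and visit as a factor, or a bootstrap that resamples women;
- PPV and NPV are not pooled over follow-up visits;
- agreement, including the kappa already planned in 2.2.7, is the main follow-up measure, and the logistic odds ratio is supportive.

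The change is to wording and analysis code only; it needs no more women or samples. The cost is wider intervals. Cross-visit intervals widen by the √DE factors above. By-visit sensitivity will be imprecise late in follow-up: at 10% positivity there are 138 x 0.10 = 13.8 positives, and even the simple formula gives a half-width of 1.96 x √(0.09/13.8) = 16 points. That is why exact or Wilson intervals are needed at those visits, and why a clustered cross-visit estimate is useful beside them.

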#### 2.6.2. Interim Analysis

Not applicable.

#### 2.6.3. Methods for Additional Analyses (e.g., Subgroup Analyses)

Not applicable.

#### 2.6.4. Methods in Analysis to Handle Protocol Non-Adherence and Any Statistical Methods to Handle Missing Data

The study is an ancillary study embedded in the PyraPreg trial and has the same sampling points as defined in the PyraPreg trial. Only an additional blood sample will be collected at each visit for the test. In case missing data occur during a visit, the whole data set of a participant at this visit will be removed from the analysis. This removal will be compensated by a slight over recruitment in the number of study participants. Nevertheless, a missing visit will not affect the data analysis of other visits of the participant.

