#### 2.2.2. Intervention

Both RDT and/or microscopy will be performed as part of the routine diagnostic procedures in place at the study sites. RDT will be performed according to the manufacturer procedures. Thin and thick blood films will be prepared and Giemsa stained. Blood slides will be independently read by 2 expert microscopists. Parasite density will be calculated by counting the number of asexual parasites per 500 leukocytes in the thick blood film, based on an assumed WBC of 8000/µL by light microscopy at 1000× magnification. In addition to routine diagnostic procedures in place, an additional blood sample (preferably finger prick blood) will be collected for test evaluation (index and reference tests). Blood samples will be properly labelled with patients’ initials, inclusion number, protocol number, scheduled study visit, and the date of the sampling. For the index test (mini-dbPCR-NALFIA) <20 μL of blood (collected in an EDTA tube) is needed. For reference testing (qPCR), three blood spots will be collected on Whatman 3 filter paper [31]; one sample for qPCR, the second and third sample for QC procedures (10%) or back-up.

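### The missing-data rule drops a woman's whole visit when any data are missing, so valid NALFIA–qPCR pairs can be lost from the primary comparison, and over-recruitment restores only the numbers

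*Protocol article*

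**What the plan says.** Section 2.6.4 fixes the handling of missing data: "In case missing data occur during a visit, the whole data set of a participant at this visit will be removed from the analysis". It continues: "This removal will be compensated by a slight over recruitment in the number of study participants". No percentage is given. The deletion is confined to the visit concerned, since "a missing visit will not affect the data analysis of other visits of the participant".

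The rule bears on the primary outcome in section 2.2.7: "We will report sensitivity, specificity, negative, and positive predictive values (primary outcome) of the mini-dbPCR-NALFIA test". Section 2.2.1 names qPCR as the reference standard and routine microscopy and/or RDT as comparators. On the comparators, section 2.2.2 says: "Both RDT and/or microscopy will be performed as part of the routine diagnostic procedures in place at the study sites". A visit record can therefore hold three or four test results, of which two (index and qPCR) are needed for accuracy against the reference.

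Section 2.6.1 plans 2 × 2 tables with 95% confidence intervals. Section 2.2.7 adds that outcomes "will be reported according to STARD principles". The article gives no separate rule for a failed or invalid index result.

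Section 2.2.9 requires 555 women for screening. For follow-up it expects around 138, a number taken from the PyraPreg trial.

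**The concern.** The unit of deletion does not match the unit of analysis. Sensitivity and specificity against qPCR need an index result and a qPCR result. The rule also makes a woman's inclusion depend on microscopy or RDT, which play no part in that table. Because the routine tests are described with and/or, it is also unclear when one that was not done counts as missing.

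Over-recruitment is presented as compensation, but extra women replace numbers only. If visits go missing more often at low parasite density, for example, the women left remain unrepresentative however many are added. Section 1 gives low peripheral parasitaemia as the reason for studying this test in pregnancy, so such a link is plausible, though the article does not show it.

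Finally, a 2 × 2 table has no cell for a test that gave no result. If failed NALFIA runs are handled under section 2.6.4, they leave the tables, and the accuracy reported applies to tests that worked.

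**Working it through.** **Inputs from the protocol article.** N = 555 and prevalence 25% (section 2.2.9). Sensitivity 0.90: "The sensitivity and specificity of the mini-dbPCR-NALFIA are assumed to be at least 90" per cent (section 2.6.1). Precision formula p ± 1.96 × √[p(1 − p)/n] (section 2.2.9).

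**Assumptions.** The article gives no half-width, missingness rate or failure rate. I assume a half-width of 5 points to reproduce 555, 3% missing independently for each test, and index failure rates of 2%, 5% and 10%.

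**Step 1: the plan's own figure.** n = 1.96² × 0.90 × 0.10 / 0.05² = 138.3 infected women. Then 138.3 / 0.25 = 553.2 or, rounding up first, 139 / 0.25 = 556. The stated 555 lies between these, so it appears to be the requirement before any allowance for lost records.

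**Step 2: precision under the rule and under pairwise exclusion.** Infected women expected: 555 × 0.25 = 138.75. With k tests required, the share of visits lost is 1 − 0.97^k, the infected women remaining are 138.75 × 0.97^k, and the half-width is 1.96 × √(0.09/n).

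| Results required | Visits lost | Infected women left | Half-width (points) |
|---|---|---|---|
| Nothing missing | 0% | 138.75 | 4.99 |
| Index + qPCR only (pairwise) | 5.9% | 130.5 | 5.15 |
| Three tests | 8.7% | 126.6 | 5.23 |
| Four tests | 11.5% | 122.8 | 5.31 |

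The fair contrast is the rule against pairwise exclusion, since pairwise exclusion also loses some women. From unrounded values that difference is 0.08 points (three tests) to 0.16 points (four tests).

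**Step 3: index failures, if treated as missing.** Suppose a share f of index runs in infected women fail at random. Sensitivity among valid results stays at 90%. The share of infected women detected is 0.90 × (1 − f):

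- f = 2%: 0.90 × 0.98 = 88.2%
- f = 5%: 0.90 × 0.95 = 85.5%
- f = 10%: 0.90 × 0.90 = 81.0%

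These are two different estimands. The gap between them is not bias in sensitivity among valid results.

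**Step 4: when bias does arise.** Suppose 25% of infections are low density, with sensitivity 75% there and 95% elsewhere: 0.25 × 75% + 0.75 × 95% = 90.0%. Let failures be 20% at low density and 2% elsewhere.

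- Valid share: 0.75 × 0.98 + 0.25 × 0.80 = 0.935.
- Detected share: 0.75 × 0.98 × 0.95 + 0.25 × 0.80 × 0.75 = 0.848.
- Sensitivity among valid results: 0.848 / 0.935 = 90.7%, which is 0.7 points too high.

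With failure rates of 10% and 2%, and of 30% and 5%, the same calculation gives 90.3% and 91.1%. Under these assumptions the upward bias is about 0.3 to 1.1 points. N does not enter the formula, so over-recruitment leaves it unchanged.

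**The case against.** The defence has several good points.

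- **Failed runs.** A reader might infer that the rule hides index-test failures. The text does not say so. It speaks of missing data and a missing visit, directly after noting that one extra blood sample is taken per visit, so it may mean absent samples or visits. Details on invalid results may be in a full protocol or analysis plan that is not shown, and STARD reporting could still disclose the counts. This stands. What remains is conditional: the article gives no other rule for such results, and disclosing counts does not change who enters the tables.
- **Bias.** A reader might take 90% against 85.5% as bias. It is a change of estimand. Bias needs missingness related to density or result, which the documents do not establish.
- **The 555.** A reader might conclude that 555 is wrong for want of an allowance. An uninflated 555 is consistent with over-recruitment added on top, and reproducing it rests on a half-width that the article does not state. The fair remark is that the top-up is unquantified.
- **Size.** Four required tests is the upper case, given the and/or wording. Section 2.2.2 also provides spare blood spots for QC or back-up, which should limit qPCR losses. The precision cost against pairwise exclusion is small.
- **Reversibility.** The rule removes records from the analysis. Nothing says they are erased from the database.

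None of this meets two points: the deletion is stated per visit, not per comparison, and added numbers cannot undo selection. Nor is a top-up described for the follow-up cohort.

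**Conclusion.** The point holds as a should-fix. As written, section 2.6.4 can discard valid NALFIA–qPCR pairs because an unrelated comparator result is missing, and its remedy addresses numbers only. The follow-up cohort of about 138 has no stated means of top-up.

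The avoidable loss of precision is small: 0.08 to 0.16 points of half-width at an assumed 3% missing per test. Whether selection bias occurs, and how large it is, cannot be settled from the article. The assumed density-related scenarios give 0.3 to 1.1 points. If failed NALFIA runs are treated as missing, the results describe valid tests only. In that case 90% sensitivity would go with 88.2%, 85.5% or 81.0% of infected women detected at 2%, 5% or 10% failures.

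The documents do not support saying that failures are concealed, that sensitivity is biased by several points, or that the sample size is in error.

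**What to change.** Amend section 2.6.4, before the data are analysed, as follows:

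1. Exclude per comparison instead of per visit. Use every woman with both index and qPCR results for accuracy against the reference, and every available pair for comparisons with microscopy or RDT.
2. Report the number of invalid index and invalid reference results.
3. Add a sensitivity analysis that counts invalid NALFIA results as incorrect, beside the analysis of valid results.
4. Remove the statement that over-recruitment compensates for deletion, and report precision at the number actually analysed.

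The cost is revised wording and one extra table, with no new samples or visits. Accuracy in the sensitivity analysis may be slightly less favourable.
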